### Design

This study comprised a stepped wedge, cluster randomised controlled trial that was conducted in two phases on the basis of student population (Study 1 = secondary school age participants; Study 2 = primary school age participants). Stepped wedge designs are similar to cross-over trials, however only involve uni-directional cross-over resulting in all participants receiving the intervention by the conclusion of the trial. The waiting list for the “Girls on the Go!” program was used to generate the control period. The intervention program was designed to be delivered to a group of participants from the same school at the same time, thus randomising students in clusters (school) was seen as an appropriate unit of randomisation.

A total of 12 schools that requested the program were separated into Study 1 or 2. Within each study, schools were matched on the basis of number of students (into triplets for Study 1 and pairs for Study 2) and then randomly allocated (computer generated sequence developed by investigator blinded to school identity) to receiving the intervention immediately or having a waiting list period. Study 1 had one waiting list period of one school term, creating two steps in the stepped-wedge design (i.e. 3 schools were provided with “Girls on the Go!” each term over 2 terms–see Figure 1). Study 2 had two waiting list periods of one and two school terms, creating three steps in the stepped-wedge design (i.e. 2 schools were provided with “Girls on the Go!” each term over 3 terms–see Figure 2).

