### Procedure

#### Ethics and trial registration

The randomised control trial was prospectively registered with the Australian and New Zealand Control Trial Registry (ACTR 12610000513011). The trial was conducted in two phases that comprised Study 1 and Study 2.

Study 1 was prospectively registered with the Australian and New Zealand Control Trial Registry (ACTRN12610000513011). We then received notification of further funding to conduct this and Study 2. We submitted an amendment to our ethics application (ethics approval 10119B) to conduct Study 2 with the Monash Health Human Research Ethics Committee as the population of Study 2 and study design only varied slightly from Study 1 (Study 1 involved high school students and had a stepped wedge design of 3 schools being provided with the intervention per term, while Study 2 involved primary school students and had a stepped wedge design of 2 schools being provided with the intervention per term). We then amended the Australian and New Zealand Control Trial Registry so that the sample size listed on the registry was increased from 60 to 120 participants.

#### Study 1

High schools that contacted the Greater Dandenong Community Health Service in 2010 to receive the “Girls on the Go!” program that year were notified of the research and that their school’s placement on the waiting list that year would be determined at random. School welfare officers and teachers forwarded to the Greater Dandenong Community Health Service the list of student names who they determined met the study and program inclusion criteria. An investigator (LT) gained consent from participant’s parents (with assent from the participant) to participate in the research from all referred students. This investigator administered the data collection surveys at baseline and follow-up assessments at the time points indicated (Figures 1 and 2). The program was provided to schools in the order determined by the matched, random allocation sequence.

#### Study 2

The same recruitment and data collection approaches were used for study 2, though with recruitment derived from primary schools, and the addition of one further follow-up assessment.

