### Analyses

The effect of being exposed to the “Girls on the Go!” program will be examined using a linear mixed model analysis approach, suitable for analysing longitudinal data where there is likelihood of missing data or loss to follow-up. The model that will be constructed to conduct this analysis will require construction of an independent variable, labelled “Girls on the Go”. This variable will be coded a 0 for observations where the group had not yet been exposed to the “Girls on the Go!” intervention (e.g. In study 1; at baseline for all schools and also at the first follow-up assessment but only for schools in the “Waiting List” period–see Figure 1), and 1 for observations where the participants had already received the “Girls on the Go!” intervention (e.g. In study 1; at the first follow-up assessment for schools in the first “Girls on the Go” period and also for all schools at the second follow-up assessment). Raw summative outcome measurement scores will be used as the dependent variables.

The mixed model analysis will involve investigating the effect of the “Girls on the Go” variable on the dependent variable, adjusting for assessment number (to account for the effect of time). The “Girls on the Go” variable will be entered into the model as a fixed factor, while assessment, student and school will be entered as random factors. Assessment will be nested within student which will be nested within school which will create a 3-level model that takes into account the longitudinal, clustered nature of data collected in this study. Maximum likelihood methods of estimation will be employed to address issues of missing data under the assumption of Missing At Random.

To investigate whether the effect of the “Girls on the Go!” program was sustained, a “Girls on the Go” by assessment interaction effect will be added to the same analysis models. A significant interaction effect in these models will indicate whether any changes brought about at the initial post-“Girls on the Go!” follow-up assessment were sustained. We will also examine the data from the group that received the “Girls on the Go!” program first and compare student results between the first and subsequent post-intervention follow-up assessments in isolation using linear regression clustering data by individual student.

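### The test of a sustained effect crosses the programme with calendar assessment, not time since the programme, so it does not isolate fading; in Study 1 it is aliased or shows half of a real loss

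*Protocol article*

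**What the plan says.** The Design section gives Study 1 two start groups of three schools: "Study 1 had one waiting list period of one school term, creating two steps in the stepped-wedge design". Study 2 has three start groups of two schools, and the Procedure section (Study 2) describes "the addition of one further follow-up assessment".

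The Analyses section codes the programme variable 0 "at baseline for all schools and also at the first follow-up assessment but only for schools in the “Waiting List” period". It is coded 1 for the first-start schools at the first follow-up and "also for all schools at the second follow-up assessment". The model is fitted "adjusting for assessment number (to account for the effect of time"), and the random structure is described thus: "while assessment, student and school will be entered as random factors".

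For durability, a programme "by assessment interaction effect will be added to the same analysis models". The reading is fixed too: "A significant interaction effect in these models will indicate whether any changes brought about at the initial" post-programme follow-up were sustained. A second look follows, in which the first-start group alone is used to compare its first with its later post-programme surveys, by linear regression clustered on student.

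**The concern.** Whether an effect is sustained is a question about time since the programme. The interaction is indexed by assessment number, which is study time. The two coincide only within one start group. At Study 1's second follow-up the girls who finished a term ago and those who have just finished have the same programme code and the same assessment number. A product of those two variables takes one value for both groups, whether assessment is treated as fixed or random.

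Two errors could follow. Real fading is diluted, so a non-significant result could be taken as a lasting effect. A common change over time that is not a straight line can also be reported as fading. Such a change is plausible: low self-esteem is one of the referral criteria, so some regression to the mean after baseline may occur. The Background itself notes that some similar programmes did not show lasting benefit, so durability matters to readers.

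**Working it through.** The plan states no figure for this test, so there is none to reproduce. The check builds the design from the coding above.

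**Inputs from the document.** Study 1 exposure over three assessments: 0,1,1 (first start) and 0,0,1 (waiting list), three schools each. Study 2 over four assessments: 0,1,1,1; 0,0,1,1; 0,0,0,1, two schools each, inferred from Design and Procedure because Figure 2 is not shown. About 10 girls per school; ICC 0.33 (Power analysis).

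**Assumptions, not in the document.** Total variance 1, split as school 0.33, girl 0.27, residual 0.40; a loss of 0.5 SD by the second post-programme survey; alternatively no loss but a common rise of 0.3 SD after baseline that stays; complete data. A school's mean then has shared variance 0.33 + 0.27/10 = 0.357 and per-assessment variance 0.40/10 = 0.04, divided by 3 schools per group in Study 1 and 2 in Study 2.

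**Estimability (fixed-effect columns and rank)**

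| Model | Study 1 | Study 2 |
|---|---|---|
| Categorical assessment + programme | 4, rank 4 | 5, rank 5 |
| Same + programme by assessment | 6, rank 4 | 8, rank 6 |
| Linear assessment + programme + product | 4, rank 4 | 4, rank 4 |
| Categorical assessment + post-programme indicators | 5, rank 5 | 7, rank 7 |

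In Study 1 exposure varies only at the first follow-up, so the categorical interaction adds no estimable parameter. Adding a linear product to categorical assessment is aliased as well (5 columns, rank 4). In Study 2 one contrast is gained, second against first follow-up, and it mixes girls at their first and second post-programme surveys.

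**Linear form, Study 1.** Write m(t,x) for the mean at assessment t with exposure x, effect θ at first and θ - δ at second post-programme survey. The product coefficient is

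γ = [m(2,1) - m(1,1)] - [m(1,0) - m(0,0)].

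- Real loss, no period change: m(2,1) = ½(θ - δ) + ½θ = θ - δ/2 and m(1,1) = θ, so γ = -δ/2. For δ = 0.5, γ = -0.25. Generalised least squares gives the same ratio of 0.500 at every within-school correlation from 0 to 0.99.
- No loss, common rise c after baseline that stays: γ = [(c + θ) - (c + θ)] - [c - 0] = -c. For c = 0.3, γ = -0.30.

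**Expected coefficients, standard errors and chance of significance** (normal test, no school-by-term variation)

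| | Study 1 linear product | Study 2 linear product | Study 1 second minus first | Study 2 second minus first |
|---|---|---|---|---|
| Standard error | 0.200 | 0.111 | 0.225 | 0.157 |
| 0.5 SD loss: expected | -0.25 | -0.154 | -0.50 | -0.50 |
| 0.5 SD loss: significant | 24% | 28% | 60% | 89% |
| Plateau, no loss: expected | -0.30 | -0.184 | 0 | 0 |
| Plateau, no loss: significant | 32% | 38% | 5% | 5% |

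Study 2's linear ratio for a one-off loss is 0.154/0.5 = 0.31. For a loss that grows each term it is about 0.50 to 0.54. The single Study 2 categorical contrast expects about -0.25 to -0.29 for the 0.5 SD loss.

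**The other planned look.** Within-girl standard error in the first-start group: √(2 × 0.40/30) = 0.163 in Study 1 and √(2 × 0.40/20) = 0.20 in Study 2. Power for the 0.5 SD loss is about 86% and 71%, provided nothing else changes between the two surveys. Any common change between them enters the estimate in full.

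**Sensitivity of the power figures.** With a t reference on 4 degrees of freedom, the 60% and 89% become about 40% and 67%. Moving 0.05 of the school variance to school-by-term variation gives about 33% and 58% (normal) or 22% and 38% (t). The linear product weakens as well: per-assessment variance rises from 0.04 to 0.09, so its standard errors grow by √(0.09/0.04) = 1.5 to 0.300 and 0.166, and its power falls to about 13% and 15%.

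**The case against.** The strongest reply is that durability does not rest on the interaction alone. The first-start comparison is indexed by time since the programme and has good nominal power. That stands, and a reader who inferred that the plan has no other look at durability would be wrong. But the comparison has no concurrent control and cannot tell fading from calendar change, so it does not make the interaction valid.

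Second, the text calls assessment a random factor and leaves its fixed form open, so the statement that the test is not estimable is conditional on categorical coding. That also stands. Neither fixed form isolates fading, however, and a random form does not help, because the product still has one value for all exposed girls at an assessment.

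Third, a reader might infer that the interaction carries no information on durability. That goes too far: the linear form reflects half of a real loss in Study 1. A reader might also take it as the primary test of persistence, or think the main effect is compromised. The document does not rank the two durability analyses, the stated hypothesis concerns improvement relative to the waiting list, and this point leaves the main model untouched.

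Fourth, the remedy has a weakness of its own. If the effect is fully sustained but 0.3 SD larger in later-start schools, the Study 1 contrast expects -0.30, a false fade. The programme description allows elements and duration to be adapted to the group, so this is not idle.

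**Conclusion.** The point holds as a should-fix. The planned interaction does not measure what its stated reading claims. In Study 1 it is aliased with categorical assessment, or with a linear trend it expects exactly half of a real loss and misreads a common plateau as fading of the same size. In Study 2 it mixes times since the programme, and the linear form shows about 0.3 of a one-off loss.

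The aliasing follows from the coding alone. The factor of one half needs equal start groups, complete data and a random-intercept type of covariance; unequal groups or missing data would shift it somewhat. The standard errors and power rest on assumed variances and an assumed loss, and 60% and 89% are illustrative upper values.

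**What to change.** In Analyses, replace the programme-by-assessment interaction by indicators for the first, second and (Study 2) third post-programme assessment. Enter assessment as a fixed category, with school and student as random effects. Test durability as second minus first, and in Study 2 also third minus first. In Study 1 this uses the randomised contrast between start groups at the second follow-up. Keep the first-start comparison as supportive, and state that it is uncontrolled for calendar time.

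The cost is revised wording and one recoded variable, with no new data. The plan should state the downsides: one extra parameter in Study 1 and two in Study 2; a slightly larger standard error in Study 1 (0.225 against 0.200 under the assumed variances); and the assumption that the initial effect is the same in each delivery term. With six schools per study, any power quoted should allow for school-by-term variation and a small-sample reference distribution.

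### The planned test for a sustained effect runs on study time instead of time since the programme, so it cannot answer the durability question

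*Protocol article*

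**What the plan says.** The Analyses section defines a 0/1 exposure variable. In Study 1 it is 0 "at baseline for all schools and also at the first follow-up assessment but only for schools in the “Waiting List” period"; exposed observations are coded 1, namely those "at the first follow-up assessment for schools in the first “Girls on the Go” period and also for all schools at the second follow-up assessment". The main model estimates the exposure effect "adjusting for assessment number (to account for the effect of time"). The model is further described as having exposure as a fixed factor, "while assessment, student and school will be entered as random factors". Whether assessment is categorical or linear is not stated.

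For durability, "a “Girls on the Go” by assessment interaction effect will be added to the same analysis models". The stated reading is: "A significant interaction effect in these models will indicate whether any changes brought about at the initial" post-programme follow-up lasted.

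A second analysis takes only the schools treated first and compares their first with their later post-programme assessments "in isolation using linear regression clustering data by individual student".

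On layout, the Design section says "Study 1 had one waiting list period of one school term, creating two steps in the stepped-wedge design", with three schools starting in each term. Study 2 has three steps of two schools and, according to the Procedure section, one further follow-up.

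**The concern.** Durability is a question about time since the programme. The interaction instead asks whether the exposed-minus-unexposed difference changes with assessment number. In a stepped-wedge layout the two clocks differ, because schools at the same assessment finished the programme at different times.

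Three consequences follow. The term may have nothing to estimate, or may estimate a blend of durability and time trend. The conclusion is tied to significance with no direction given, although an effect that lasts predicts an interaction of zero when time has no non-linear component. The supporting analysis uses the right clock but has no comparison group and treats students, not schools, as the clusters. The risk is a wrong statement, in either direction, about whether the benefit persists.

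**Working it through.** The protocol gives no figure for this test, so there is none to reproduce. The check uses its own coding.

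**Inputs from the article.** Exposure coding (Analyses); two sequences of three schools and three sequences of two (Design); baseline plus two follow-ups in Study 1 and one more in Study 2 (Analyses, Procedure); ICC 0.33 and 10 girls per school (Power analysis).

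**Assumed for illustration.** Total variance 1, school variance 0.33, and the remaining 0.67 split into student 0.402 and residual 0.268 (40% of 0.67). An alternative split of 0.30 and 0.37 is named where used. Effect sizes and time shifts are also assumed, except 1.5 SD, which is the Power analysis figure.

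**1. Study 1 layout**

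| Schools | Baseline | Follow-up 1 | Follow-up 2 |
|---|---|---|---|
| Treated first (3) | 0 | 1, just finished | 1, one term past |
| Waiting list (3) | 0 | 0 | 1, just finished |

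In Study 2 the sequences are 0,1,1,1; 0,0,1,1; and 0,0,0,1.

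**2. Categorical assessment.** Study 1 has 4 non-empty exposure-by-assessment cells. Intercept, 2 assessment effects and 1 exposure effect use all 4. Adding the interaction gives 6 columns, still of rank 4: 4 - 4 = 0 degrees of freedom. Only follow-up 1 has both exposed and unexposed schools. Study 2 has 6 non-empty cells and 1 + 3 + 1 = 5 main-effect parameters: 6 - 5 = 1 degree of freedom (8 columns, rank 6). That one contrast compares follow-up 1 with follow-up 2, where exposed schools again differ in time since the programme. Complete loss of a 1.5 SD effect after one term shows as about -0.85.

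**3. Linear assessment, Study 1.** With y = a + bt + cX + iXt, the expected changes are:

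- treated first: b + c + i, then b + i;
- waiting list: b, then b + c + 2i.

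Two contrasts estimate i:

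- A = (treated first, second change) - (waiting list, first change);
- B = (waiting list, second change) - (treated first, first change).

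Generalised least squares with school and student random intercepts gives results equal to their average. B compares two effects measured just after the programme, so it carries no information on durability.

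| Truth | A | B | Interaction |
|---|---|---|---|
| Effect d sustained, no trend | 0 | d - d = 0 | 0 |
| Effect d lost after one term | -d | d - d = 0 | -d/2 |
| Effect d sustained, one-off shift s after baseline | -s | d - (d + s) = -s | -s |

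So complete loss of 1.0 SD gives -0.50, and of 1.5 SD gives -0.75. A shift of s = 0.3 gives -0.30 whatever d is. In Study 2, complete loss of 1.5 SD gives -0.46 (0.46/1.5 = 31% of it), and a 0.3 SD shift gives about -0.18.

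**4. Reading a null result.** If a 1.5 SD effect halves after one term, the Study 1 linear interaction is -0.375. With residual variance 0.37 its standard error is 0.192, a ratio of 0.375/0.192 = 1.95. A loss of 0.75 SD would thus be missed about half the time.

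**5. Analysis of the first-treated schools.** Let v be the school-by-term variance and e = 0.268. For 3 schools and 30 girls, the ratio of the true to the student-level variance of the change is (2v/3 + 2e/30)/(2e/30) = 1 + 10v/e.

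| Assumed share of school variance | v | Ratio | Type I error at nominal 5% |
|---|---|---|---|
| 5% | 0.0165 | 1.62 | 12% |
| 10% | 0.033 | 2.23 | 19% |
| 20% | 0.066 | 3.46 | 29% |

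**6. Time-since-programme indicators.** With categorical assessment the design is full rank: 5 of 5 columns in Study 1, 7 of 7 in Study 2. A sustained 0.5 SD effect with the 0.3 SD shift returns 0.5 at every post-programme assessment. Complete loss of 1.0 returns 1, then 0. In Study 1 the standard errors are about 0.19 SD (first effect) and 0.32 SD (later effect).

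**The case against.** Several points on the other side stand.

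- **Direction.** A reader might infer that the protocol takes significance as proof that the effect lasted. The sentence says only that the result will show whether it did. The fair criticism is that no direction is given.
- **Estimability.** A reader might infer that the interaction cannot be fitted in Study 1 at all. That holds only for categorical assessment. The article does not state the coding, lists assessment among the random factors, and may leave the detail to an analysis plan. With linear coding the Study 1 model is full rank (4 of 4).
- **Size of the bias.** The -0.30 SD is the assumed shift handed back. The documents report no such shift, and without a non-linear trend a sustained effect gives 0. Even with the shift, 0.30 against a standard error of about 0.16 reaches significance only about 45% of the time. That a sustained effect will be declared lost is therefore not established.
- **Second analysis.** It does follow time since the programme. The type I error rates above depend on variance shares that the documents do not give.
- **Importance.** The hypothesis concerns improvement relative to the waiting list. Durability is a follow-on question.

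None of this restores the interaction. Under either coding it runs on study time. The second analysis cannot separate loss of effect from term effects, and in Study 1 no unexposed school remains at the second follow-up to help it.

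**Conclusion.** The concern holds in limited form. That the interaction uses the wrong clock follows from the protocol's own coding and needs no assumption. The degrees of freedom (0 in Study 1, 1 in Study 2) are exact for categorical assessment. The recovery of half of a complete loss in Study 1 holds for linear assessment with school and student random intercepts. The shift-driven values and the type I error rates are illustrations that rest on assumed trends and variances. Tying the conclusion to significance is unsafe because maintenance would have to be read from a null result in six schools. Severity is should-fix: statements about durability are affected, while the main programme effect is not touched by this point.

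**What to change.** Replace the interaction with indicators for the first, second and, in Study 2, third post-programme assessment. Keep assessment as a fixed categorical factor, with the same student and school random effects. Report each effect, and the later-minus-first difference, with 95% confidence intervals in place of a significance rule. A rule that calls the effect sustained only when the later interval excludes zero would be too blunt: at a standard error of 0.32, a true 0.5 SD effect (0.5/0.32 = 1.56) would pass only about 35% of the time.

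State two limits for Study 1. The later effect is imprecise (about 0.32 against 0.19 SD under the assumed variances). It also relies on the first-assessment effect being equal across terms: if that effect were 1.5 SD in the first term and 0.75 SD in the second with no loss, the later-minus-first estimate would be +0.75 instead of 0.

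Label the regression on the first-treated schools as descriptive. Clustering it by school would not rescue it, since 3 or 2 clusters are too few for cluster-robust standard errors.

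The cost is a few lines of analysis text and no new data.

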### Power analysis

Analysis of data from the pilot study indicated that the effect of the “Girls on the Go!” program on participant self-esteem was very strong (ie. Change in outcome is 1.5 times the width of the standard deviation). Assuming 80% power, only 10 participants per group will be required in a standard randomised trial with randomisation of individual participants. This study will be a cluster randomised trial however to account for a variance inflation factor (design effect) of 3 (where average size per cluster is n =10, and the ICC is assumed to equal 0.33) then a total of 120 participants in both the primary (n = 60) and secondary (n = 60) schools will be required.

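### In Study 2 the supplementary maintenance comparison leaves out the second step's two schools, although they too have a first and a later post-programme survey

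*Protocol article*

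**What the plan says.** The last paragraph of the Analyses section plans two ways of asking whether the effect lasts.

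- The first is an exposure-by-assessment term in the mixed model: the "interaction effect will be added to the same analysis models". Those models take all schools and all assessments.
- The second is introduced as an addition: "We will also examine the data from the group that received the “Girls on the Go!” program first". Students in that group are compared between the "first and subsequent post-intervention follow-up assessments in isolation using linear regression clustering data by individual student".

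The second rule is worded once, for both studies. The section's worked examples of exposure coding come from Study 1.

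**The concern.** A rule that suits a two-step design is carried unchanged to a three-step design. With two steps, the first-treated group is the only one that can be seen more than once after the programme. With three steps, the middle group can be too. If so, the planned comparison sets aside schools that have exactly the pair of measurements it needs.

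This matters because a maintenance claim rests on seeing little decline. The wider the interval, the easier it is to find no significant change and the less that finding says. In addition, with one step only, time since the programme and calendar term coincide, so a reader cannot see whether the change looks different in another term.

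**Working it through.** The plan gives no precision or sample size for this comparison, so there is no stated figure to reproduce. The Power analysis section supplies only the cluster size.

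**Inputs**

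- Study 1 steps (Design): "3 schools were provided with “Girls on the Go!” each term over 2 terms".
- Study 1 exposed observations (Analyses): "at the first follow-up assessment for schools in the first “Girls on the Go” period and also for all schools at the second follow-up assessment". So Study 1 has a baseline and two follow-ups.
- Study 2 steps (Design): "2 schools were provided with “Girls on the Go!” each term over 3 terms".
- Study 2 assessments (Procedure, under Study 2): "the addition of one further follow-up assessment". So Study 2 has a baseline and three follow-ups.
- Girls per school (Power analysis): "where average size per cluster is n =10, and the ICC is assumed to equal 0.33". This agrees with 60 girls in 6 schools per study, 60/6 = 10.

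**Step 1: post-programme surveys by step.** This is inferred from the text, since Figure 2 is not shown. Pairs = later post-programme surveys per girl × schools × 10.

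| Study | Step | Schools | Post-programme at follow-up | First-to-later pairs |
|---|---|---|---|---|
| 1 | 1 | 3 | 1, 2 | 1 × 3 × 10 = 30 |
| 1 | 2 | 3 | 2 | 0 |
| 2 | 1 | 2 | 1, 2, 3 | 2 × 2 × 10 = 40 |
| 2 | 2 | 2 | 2, 3 | 1 × 2 × 10 = 20 |
| 2 | 3 | 2 | 3 | 0 |

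Study 1 uses all 30 of its pairs. Study 2 uses 40 of 60. For the one-term change, Study 2 uses 20 girls in 2 schools where 40 girls in 4 schools have the data.

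**Step 2: precision of the one-term change**, in SD of change, with no dropout and school clustering ignored.

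- SE = 1/√n: 1/√20 = 0.224 as planned; 1/√40 = 0.158 with both steps.
- Ratio = √(40/20) = 1.41. Using both steps lowers the SE by 1 − 1/1.41 = 29%.
- Minimum detectable change (paired t, two-sided 5% assumed, 80% power): 0.66 falls to 0.45 SD of change.
- The Participants section allows 8 to 12 per school. For equal school sizes the ratio does not move: √(32/16) = √(48/24) = 1.41.

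**Step 3: precision of first against the mean of later surveys**, assuming equal correlation between surveys. In a common unit, the variance per girl is 1 + 1/2 = 1.5 for step 1 (two later surveys) and 1 + 1 = 2 for step 2 (one later survey).

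- Precision from step 1: 20/1.5 = 13.3. From step 2: 20/2 = 10.
- SE ratio = √(23.3/13.3) = 1.32. Using both steps lowers the SE by about 24%.

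The two-term change exists only in step 1, so it gains nothing.

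**Step 4: does the interaction answer the same question?** Take assessment as categories.

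- Study 2 has six observed exposure-by-assessment cells: one at baseline, two at follow-up 1, two at follow-up 2, one at follow-up 3. Main effects use 4 + 1 = 5 parameters. One interaction contrast is left, the effect at follow-up 1 against that at follow-up 2. At follow-up 2 the exposed schools mix step 1, one term after the programme, with step 2, which has just finished.
- Study 1 has four cells and 3 + 1 = 4 parameters, so nothing is left.

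**Step 5: what adding the second step can identify.** Let d1 and d2 be the change in the first and second term after the programme, and t12 and t23 the calendar change between follow-ups 1 and 2 and between 2 and 3.

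- Step 1 shows d1 + t12 and d2 + t23. Step 2 shows d1 + t23.
- Three observed changes, four unknowns. Only d2 − d1 and t12 − t23 can be recovered; d1 alone cannot.

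**Step 6: school clustering.** The planned regression clusters by student only. With design effect DE = 1 + 9 × ICC, the true error of a nominal 5% test is about 2[1 − Φ(t/√DE)]. For an assumed school ICC of change of 0.05 to 0.33, DE runs from 1.45 to 3.97. The error is about 8% to 29% with 2 schools and about 9% to 31% with 4.

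**The case against.** The strongest reply is that maintenance is assigned first to the interaction, fitted to all six schools, and that the isolated comparison is an extra. That stands as far as it goes. A reader might infer that two schools are left to carry the maintenance claim, or that the second step's last survey is thrown away. The text supports neither: the data are left out of this comparison, not out of the plan. But the reply does not dispose of the point. The one interaction contrast available in Study 2 is not a contrast of first with later post-programme scores, so the isolated comparison is the only planned analysis that makes it directly.

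A reader might also infer that adding the second step would separate change after the programme from calendar change. It would not. Drift common to both terms stays confounded with d1, and the comparison has no untreated group. Showing the steps separately can reveal drift that differs between terms, and no more.

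Two further objections stand. The 1.41 ratio belongs to the one-term change, which the plan does not single out; for first against the mean of later surveys the ratio is 1.32. And adding schools does not cure the neglect of school-level clustering: the interval gets narrower but remains too narrow.

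Finally, the first-treated group has the longest follow-up and a single schedule, so using it alone is a defensible simplification for a supportive look. In Study 2 that simplification costs precision which the scheduled surveys could supply.

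**Conclusion.** The point holds for Study 2 only, and as a loss of available information in a supplementary comparison. About half of the girls who can inform the one-term change are omitted (20 of 40, in 2 of 4 schools), so the standard error is 1.32 to 1.41 times what it need be, depending on the contrast. Study 1 and the two-term change are unaffected.

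This rests on 10 girls per school, no dropout, school clustering ignored, equal correlation between surveys for the 1.32, and a Study 2 schedule read from the Design, Procedure and Analyses sections because Figure 2 is not shown. If that figure shows the second step not surveyed at follow-up 3, the point falls.

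It does not show that the sustained-effect analysis as a whole depends on two schools, or that a wider comparison would be free of calendar effects.

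**What to change.** For Study 2, reword the isolated comparison as follows:

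- Include every girl with at least two post-programme assessments.
- Use terms since the programme as the time scale. Estimate the one-term change from steps 1 and 2 together and the two-term change from step 1.
- Account for school as well as student.
- Show the one-term change separately by step.
- State that the comparison is uncontrolled, that the by-step display can reveal drift differing between terms, and that it cannot remove drift common to both.

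Leave the Study 1 choice of group as it is.

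No new data are needed; only the analysis wording changes. The one cost is candour about width. If school means are the unit, two schools leave 1 degree of freedom (critical value 12.71) and four leave 3 (3.18). With four schools the 95% half-width is then about 0.50 to 1.00 SD of change for a school ICC of 0 to 0.33. That is wider than the 0.47 which the student-only analysis would show from two schools, but the student-only figure ignores school. On the same school-level footing, two schools would give 2.84 to 5.66.
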